#### *1.1.1 Conceptual framework*

The modified socioecological framework outlines the four interacting levels of personal and environmental factors that impact maternal and child health. The structural level refers to systems that evoke socioeconomic/cultural policies and norms; the community level pertains to care settings and resources that impact women's access; the interpersonal level is personal relationships; and the individual level is a woman's physical and mental health. Based on the framework and relevant literature, we hypothesize that, compared to CPSP/IC, Glow/GC has greater capacity to improve mental health (primary aim), result in more positive care experience (secondary aim) and decrease PTB rates (exploratory aim) by incorporating social determinants of health, peer-to-peer processes, and process-of-care factors (see Figure 1).

Figure 1. Conceptual Framework

[figure not shown]

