#### **5.1.4 Third Trimester Follow-up Interview ( $\geq 30$ weeks' gestation)**

The third trimester questionnaire will be completed with participants in both arms of the study. The goal of this interview is to check-in with the participant and collect data on the participant-reported secondary outcomes and covariates.

Third trimester questionnaire. The RRS will contact the participant to schedule a time to complete the questionnaire by telephone, at CVHPI, or at an upcoming prenatal care appointment, according to participant preference. The ideal timing for the interview will be between 30-34 weeks' gestation and a minimum of 6 weeks after the baseline interview. The questionnaire will be administered by a different RRS than the one who administered the baseline questionnaire to ensure the RRS remains masked to the participant's allocation assignment. A copy of the third trimester questionnaire (Appendices 11 and 12) will be offered to the participant so she may follow along as questions are read aloud. The RRS will keep track of the time at the start and end of the interview and note if there is an interruption to the interview lasting more than 5 minutes.

During the interview, the participant will be asked where they plan to deliver. If the facility is different from the facility reported at baseline, the RRS will ask the participant to sign a HIPAA research authorization form for the new facility if necessary, and if required, a consent to release birth hospitalization medical records to the study team.

If the participant has experienced a stillbirth or infant death at  $\geq 20$  weeks gestation, the RRS will ask if they would like to complete a final exit interview with modified questions and their information will be recorded in the REDCap database (see Appendix 17 and 18). We will review the participant's medical record to abstract the clinical data. If participants experience a pregnancy loss prior to 20 weeks, the RRS will let them know they are no longer eligible for follow-up interviews and their information will be recorded in the REDCap database; their medical record data will not be abstracted or included in the study analyses. If the participant has already given birth at the time

of the third trimester questionnaire, they will not complete the interview and the postpartum interview will be completed.

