## 7.5 Data Analysis

Primary and secondary analyses will include all participants based on treatment assignment, according to intention-to-treat principles. We expect our experimental design with allocation of treatment sequence by provider to lead to minimal imbalance at the participant level. Nonetheless we will collect data and adjust for potential confounders. Confounding information will be collected via REDCap questionnaires at baseline, 3rd trimester, and postpartum. Medical records will be linked by participant name and date of birth and abstracted after delivery to obtain data for our clinical outcomes (preterm birth and gestational age at delivery) and covariates. Maternal comorbidities will also be recorded from the medical records. Adherence will be quantified as the number of prenatal care visits in each treatment model, as opposed to initial assignment. To assess the effectiveness of different durations of participation in either treatment, we will conduct a secondary analysis limited to 1) participants who have attended at least one group or individual care session (after randomization) and 2) participants who have attended at least one group or individual care session (after randomization). For all analyses, we will first examine descriptive statistics, check modeling assumptions, and present effect estimates along with associated confidence intervals. Data analysis will be conducted while masked to treatment assignment.

**Aim 1 Hypothesis:** Women assigned to Glow/GC will have greater reduction in depressive (**1°**) and anxiety (**2°**) symptom severity at 3 months postpartum (1° time point) and in the 3rd trimester (2° time point) than women assigned to CPSP/IC.

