*Missing outcomes and covariates:* As baseline data will be collected at time of treatment assignment, and clinical outcomes will be obtained from medical record review, we do not estimate substantial missing data for Aim 3. We plan to reduce missing data for Aims 1 and 2 through our retention plan. We will record all reasons for study withdrawal and missing data. Participants lost-to-follow up will undergo medical record review for the outcomes of preterm birth and gestational age. Our mixed model analyses offer robust protection against data that are missing at random. We will assess missing data across study covariates and time points and use multiple imputation if it is appreciable. Pregnancies that end in miscarriage, abortion or fetal death prior to 20 weeks gestation will not be included in analysis.

*Heterogeneity of treatment effect (HTE):* We will assess if the effectiveness of Glow/GC compared with CPSP/IC differs by practice or patient characteristics through interaction analyses. Pre-specified analyses of treatment heterogeneity include: complications of pregnancy, parity, race/ethnicity, provider type (CNM, MD, NP). We will also conduct exploratory analyses on additional covariates (social support, site, size of practice or location, prior experiences of racism) to assess treatment differences. HTE will be assessed using interactions between

treatment assignment and each proposed effect modifier tested with a cut-point of ( $p < .10$ ) for HTE.

*Avoidance of bias:* The use of randomization of treatment initiation within practices allows us to minimize the risks of confounding and selection bias. More efficient designs with less susceptibility to bias are unfortunately not feasible in this study, as the treatment is administered at the practice level and needs to be incorporated without substantial interruption to clinical processes. To enhance generalizability of the study, we are recruiting from a diverse low-income patient population including English- and Spanish-speakers, with study staff and all assessment tools available in both languages. While we cannot mask treatment assignment to providers, participants or study staff, we will make every effort to ensure equivalent study procedures across both groups. Chart review and data analysis will be performed by study staff masked to treatment assignment to reduce ascertainment bias.

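### Section 7.5 draws adjustment covariates partly from sources collected after assignment and has no rule excluding variables that the arm can change

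*Combined protocol and SAP*

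**What the plan says.** Section 7.5 promises an intention-to-treat analysis, expects little imbalance, and then adds: "Nonetheless we will collect data and adjust for potential confounders". The next sentences give the sources, the confounding information coming from "questionnaires at baseline, 3rd trimester, and postpartum. Medical records will be linked by participant name and date of birth and abstracted after delivery". The records are to be "abstracted after delivery to obtain data for our clinical outcomes (preterm birth and gestational age at delivery) and covariates", and "Maternal comorbidities will also be recorded from the medical records", with no distinction by date of onset. Section 5.1.4 confirms the point for the third-trimester interview, which is meant to "collect data on the participant-reported secondary outcomes and covariates".

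The Aim 3 models in Section 7.5 include the covariates explicitly. The Aim 1 paragraph specifies linear mixed models and refers to a plan like that of Aim 1, that is, to itself. Section 10.0 reports that the aims were re-ordered, so this may be a leftover that points to the model now under Aim 3, but the text does not say so. No section lists the covariates or says when they must have been determined.

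Under heterogeneity of treatment effect, Section 7.5 states: "Pre-specified analyses of treatment heterogeneity include: complications of pregnancy, parity, race/ethnicity, provider type (CNM, MD, NP"). The first of these modifiers has no definition and no time window.

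**The concern.** In a comparison by assigned arm, a confounder has to be settled before assignment. A variable that the arm can alter is either part of the route by which the arm works or a consequence of it that shares causes with the outcome. Adjusting for the first removes part of the effect. Adjusting for the second can create a difference where none exists. In both cases the adjusted coefficient no longer estimates the intention-to-treat effect that Section 7.5 promises.

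The risk is concrete in this trial. Section 1.1.1 expects Glow/GC to do better "by incorporating social determinants of health, peer-to-peer processes, and process-of-care factors". Section 4.1 describes Glow/GC as supplying social support, mental health education and treatment, food, transport help and links to services. The baseline questionnaire (Section 5.1.3) covers stress, sleep, food security, loneliness and social support. If such items are asked again later, the later values are plausible consequences of the arm. The postpartum interview is also where the primary PHQ-9 outcome is measured. Section 5.1 takes maternal and neonatal morbidity outcomes from the same delivery record that is to supply covariates, and nothing separates the two uses.

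A modifier that the arm can change has a related problem: its subgroups are no longer comparable between arms, so the interaction is hard to interpret.

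**Working it through.** **1. The plan's own figure.** Inputs from Section 7.2: standardized effect 0.25, alpha 0.05, power 0.85, retention 88%. Sidedness is not stated, so two-sided is assumed.

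- n per arm = 2 × (1.960 + 1.036)² / 0.25² = 287.3, so 288. The exact t-test gives power 0.850 at 288 and 0.851 at 289 per arm.
- 578 / 0.88 = 656.8, so 657.

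The stated 289 per arm, 578 and 657 reproduce. A one-sided test would need 231 per arm, which does not match.

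**2. Timing of each covariate source.** Section 2.3 places assignment after the baseline survey, which is done by 24 weeks 6 days (Section 5.1.3).

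| Source named for confounders or covariates | When | Relative to assignment |
|---|---|---|
| Baseline questionnaire | by 24 weeks 6 days | before |
| Third-trimester questionnaire | 30 weeks or later | after |
| Postpartum questionnaire | 10–14 weeks after delivery | after; same interview as the primary outcome |
| Delivery record | after delivery | recorded after; onset may be before or after |

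What matters is when a characteristic was fixed, not when it was written down. Parity or chronic disease read from a delivery record is harmless. A social support score taken at 30 weeks is not.

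**3. Illustration: adjusting for a mediator.** The documents give no mediated share, so the share m is an assumption. With residual SD held at 1:

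- adjusted effect d = 0.25 × (1 − m)
- power = Φ(d × √(289/2) − 1.960), with √(289/2) = 12.02

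| m | d | d × 12.02 | Power |
|---|---|---|---|
| 0 | 0.25 | 3.005 | 0.85 |
| 0.20 | 0.20 | 2.404 | 0.67 |
| 0.40 | 0.15 | 1.803 | 0.44 |
| 0.60 | 0.10 | 1.202 | 0.22 |

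A covariate that carries part of the effect also predicts the outcome and reduces the residual SD. Suppose assignment shifts it by a SD and its slope on the outcome is b = 0.5. The residual SD is then √(1 − 0.25) = 0.866 and the adjusted effect is 0.25 − 0.5a. For a = 0.1, 0.2 and 0.3 the adjusted effects are again 0.20, 0.15 and 0.10, and power is 0.79, 0.55 and 0.28. The loss is smaller, but the estimate is shifted by the same amount.

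**4. Illustration: collider, true effect zero.** Suppose assignment shifts the covariate by a SD, and an unmeasured factor loads c on both covariate and outcome. Then bias = −a × c², residual SD = √(1 − c⁴), and SE = residual SD × √(2/289).

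- At a = 0.2, c = 0.5: bias = −0.05, SE = 0.968 × 0.0832 = 0.081, and two-sided type I error is about 0.095.
- Over a = 0.1 to 0.3 and c = 0.3 to 0.7, the absolute bias runs from 0.009 to 0.147 SD and type I error from 0.051 to 0.527.

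The sign follows the direction of the shift and of the loadings, so it can favour either arm.

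**The case against.** The strongest reply is that collecting a variable is not the same as conditioning on it. No covariate list exists, and no sentence puts a third-trimester or postpartum value into the primary PHQ-9 model. Covariates are placed in a model explicitly only under the exploratory Aim 3. This stands as a limit on the point: a reader might infer that the primary analysis will adjust for post-assignment variables, and the documents do not show that. It does not remove the point, because Section 7.5 commits to adjustment and in the next sentence calls the data from all three questionnaires confounding information. The stated rule points at the wrong sources, which is more than missing detail.

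A second reply is that late recording is not late onset, and the maternal comorbidities may be chronic conditions. That is correct, and the fix is worded to allow it.

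A third concerns *complications of pregnancy*. A reader might infer that this modifier is measured after assignment, or that most complications arise after enrolment. The documents support neither: the term is undefined, they give no figure on timing, and health and pregnancy history are collected at baseline (Section 5.1.3), so a pre-enrolment reading is open. The heterogeneity analysis also leaves the primary estimate untouched. What stands is that the term needs a definition.

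Finally, Section 7.2 is right that adjustment can improve precision. Covariates fixed before assignment can give that benefit without the bias.

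**Conclusion.** The point holds in this form: the adjustment rule in Section 7.5 admits variables that the arm can change, and nothing in the documents excludes them. Adjusting for such variables can bias the intention-to-treat effect in either direction. A reader might expect the bias to run towards no difference. That would follow if the only problem were a mediator carrying a beneficial effect, but the collider case can go either way and the documents do not settle which applies.

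The size of the bias cannot be derived from the documents. The fall in power from 85% to about 67%, 44% or 22% rests on assumed mediated shares of 20%, 40% and 60%, residual SD held at 1, 289 per arm and a two-sided 5% test. It shows what could be at stake and does not forecast this trial's result. The collider figures likewise rest on assumed shifts and loadings. The planned sample size is not in question.

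**What to change.** In Section 7.5:

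- Name the covariates and restrict adjustment in all primary and secondary models to characteristics fixed before assignment, whenever they were recorded. Examples are baseline PHQ-9 and GAD-7, gestational age at enrolment, parity, baseline social support, medical history, provider and due-date period. Provider and due-date period have a clear claim because assignment depends on them (Section 2.3).
- Use later variables only as auxiliary variables in multiple imputation or in an analysis labelled as mediation.
- Define *complications of pregnancy* as conditions or obstetric risk present at or before enrolment, taken from the baseline health and pregnancy history or from dated records.

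The cost is wording in the analysis plan, settled before the analysts are unmasked. Enrolment of 657 and the analysed 578 stay as they are. No new data should be needed, judging by the baseline topics in Section 5.1.3. The questionnaire appendices are not among the documents, so the team should confirm that the baseline items, or dated records, capture complications of the current pregnancy up to enrolment.

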## **2.3 Randomization**

Both comparators will be offered within each site. At each site, participating providers will be randomly assigned to one of two recruitment tracks: recruiting initially for Glow/GC or recruiting initially for CPSP/IC. The two tracks will alternate between recruitment for Glow/GC and recruitment for CPSP/IC based on prespecified six-week ranges of estimated delivery dates (EDD), for the duration of the study. Based on the provider's randomization track and the participant's due date, participants will be placed in either the Glow/GC or CPSP/IC arm (see Figure 3 for an example of the treatment assignment for Provider A, who was randomly assigned to recruit for Glow/GC for the initial 6-week period of the study). This design optimizes the number of Glow/GC sessions offered by each practice (no more than 4 concurrent groups per clinician) and is ideal for clinic flow. Because the maximum number of women

who can be enrolled in a Glow cohort is 12, after 12 have enrolled, subsequent eligible women will be allocated to CPSP.

Figure 2. Consort diagram

[figure not shown]

Randomization will be stratified by recruitment site and provider. If the site has more than one provider and can accommodate only one Glow group at a time, the first provider will be randomized to a starting comparator track and the second provider will start with the other comparator sequence. Randomization tables were generated in blocks of size 4 with Stata v16.0 using the runiform function, which utilizes the 64-bit Mersenne-Twister random number generator. RRSs will not assign participants to the Glow/GC or CPSP/IC arm until after completion of their baseline survey, at which point the RRS will inform the participant of her group assignment and enter it into the study database. The appropriate comparator assignment is determined utilizing a tool that does not reveal comparator

estimated due date ranges. To help ensure that the assessors of the primary and secondary outcomes are masked with respect to group assignment, a different staff member will conduct the third trimester and postpartum interviews and perform the medical chart abstraction.

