## **7.2 Sample Size**

We conducted sample size calculations for change in depressive symptom severity. We powered our study to detect meaningful changes in depressive and anxiety symptoms. Using an alpha of .05 and power of .85, we will be able to detect a standardized effect size of 0.25 with a sample size of 578 individuals in total (289 per arm). We are assuming a retention rate of 88% (as per our previous study and experience in the current study) and power of 85% (per PCORI's request). A standardized effect size of 0.2 to 0.3 is widely considered to be a small effect size. We therefore plan to enroll 657 participants in the study, and, with a retention rate of 88%, we will have > 85% power to detect small effect sizes for these outcomes. Adjustment for covariates in multivariable analyses for numeric outcomes may make the residual SD smaller than the raw SD, improving precision and power.

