**Aim 1 Analyses:** We will compare changes in depressive (PHQ-9) and anxiety (GAD-7) symptom severity from baseline to three months postpartum and 3rd trimester. The multivariate analyses will follow an analytic plan similar to that of Aim 1, using linear mixed models to assess primary and secondary outcomes. We will conduct separate analyses comparing symptom exacerbation from baseline to 3rd trimester and baseline to 3 months postpartum. **Exploratory analyses (1a):** Previous work among pregnant women found rates of elevated depressive symptoms were 19.9% and 17.1% for Black and Latina women, respectively, compared to 9.5% of White women. We will explore the disparities in maternal mental health for Black and Latina women in our sample. Exploratory Aim 2a will follow the same analysis plan as 1a.

**Aim 2 Hypothesis:** Women assigned to Glow/GC will report more person-centered care (**1°**), respectful care (**2°**), and prenatal care satisfaction (**2°**) than women assigned to CPSP/IC, at 3 months postpartum (1° timepoint) and in the 3rd trimester (2° timepoint).

**Aim 2 Analyses:** We will use quantitative and qualitative methods to assess patient perceptions of person-centered care, respectful care, and satisfaction with care. The quantitative analysis will follow methods similar to those described in Aim 1, using linear mixed models for the PCPC and PCMC-US, MORi, and PCSS numeric outcomes. **Exploratory analyses (2a)** will follow the same plan above for the Black and Latina subgroups. **For Aim 2b**, in-depth interviews will focus on experiences of respectful and disrespectful care during the current pregnancy or in the past, experiences of racism in care or in other settings, and barriers/enablers of accessing care or services in their family/social network. The study will generate digital audio recordings and

transcripts encrypted when in transit. Data will be entered, coded, memoed, and organized using the Dedoose software program, which allows for open coding, theoretical memoing, and detailed conceptual matrixing of transcript and memo data within and across participants. Sorting functions allow for cross-group comparison by code or characteristic and for establishing a system of inter-coder reliability. We will store all data on a secure server at UCSF, accessible only to the investigative team via password-protected, encrypted computers.

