**Aim 3 Hypotheses (exploratory):** Women assigned to Glow/GC will have lower rates of preterm birth (**primary (1°)**) and will give birth at higher gestational ages (**secondary (2°)**) than women assigned to CPSP/IC.

**Aim 3 Analyses:** We will describe simple differences in proportions of preterm birth and mean gestational age by treatment group. We will examine models comparing treatment assignment to Glow/GC versus CPSP/IC including the covariates, using logistic mixed models (for preterm birth) and linear mixed models (for gestational age), with clustering by practice and provider. We will examine assumptions of normality for the gestational age outcome, and deviations from linearity for covariates. **Exploratory subanalyses (3a):** We will explore preterm birth rates and gestational age at delivery among Black and Latina participants in each treatment arm, to examine whether Glow/GC and CPSP/IC may be more or less effective in these subgroups. These aims will be exploratory in nature, as we do not anticipate having a sufficient sample to have high power to test our hypotheses in these groups. We will assess effectiveness within subgroups based on race/ethnicity and language and report the p-value for interaction.

We will begin to code data immediately after the first phase of interviews are completed, in bimonthly data meetings that will include interview staff and co-investigators. We will take extensive notes during meetings to document emergent concepts and themes for codebook development. Codes will be developed mirroring the topics outlined in interview guides, which we will develop prior to study initiation. Regular data analysis meetings will create a constructive dialogue that both triangulate the quantitative and qualitative data collected in Aim 2. While reviewing qualitative data, we will note reoccurring themes (open coding). While completing open coding, we will write theoretical and methodological memos consistent with qualitative analysis methodologies. We will finalize a codebook and code and enter all data into Dedoose. We will review selected transcripts to check for inter-coder reliability. Staff will maintain the coding database and produce outputs for analysis and generate data summaries.

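### The primary (Aim 1) model is defined only by reference to itself, and the clustering that can be inferred for it omits the provider-by-due-date window that sets each woman's arm

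*Combined protocol and SAP*

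**What the plan says.** Section 7.5, Aim 1 Analyses: "The multivariate analyses will follow an analytic plan similar to that of Aim 1, using linear mixed models to assess primary and secondary outcomes". The paragraph names linear mixed models for PHQ-9 and GAD-7 change. It gives no random effects, cluster level, baseline handling or covariate list.

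Section 7.5, Aim 2 Analyses, points back to the same paragraph: "The quantitative analysis will follow methods similar to those described in Aim 1".

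Section 7.5, Aim 3 Analyses (preterm birth and gestational age), has the only clustering statement in the document: "with clustering by practice and provider".

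Section 2.3 randomizes each provider to a starting track. The track then alternates between Glow/GC and CPSP/IC by "prespecified six-week ranges of estimated delivery dates (EDD", and a woman's arm follows from her provider and due date. Once a Glow cohort holds 12 women, later eligible women go to CPSP. Section 4.1 describes Glow care as 8–11 sessions shared by 6–12 women within a six-week gestational range.

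Section 10.0 records that the order of the aims was changed mid-study: mental health moved from Aim 2 to Aim 1, and preterm birth became exploratory.

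Section 7.2 bases the sample size on this statement: "Using an alpha of .05 and power of .85, we will be able to detect a standardized effect size of 0.25". The evaluable total it gives is 578, split equally between the arms. Neither an ICC nor a design effect is mentioned.

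**The concern.** There are two layers. First, as written, the primary analysis has no stated model: Aim 1 refers to Aim 1, and Aim 2 refers to Aim 1. Second, filling the gap from Aim 3 gives practice and provider as the clustering levels, and in this design those are the levels that matter least to the arm comparison. Every provider contributes women to both arms, so what is common to a provider largely drops out of the difference between arms. What stays in is variation between windows within a provider. That can come from the shared Glow group and its facilitator, the calendar period, and the in-person or telehealth mode at the time. A provider-only model treats that variation as independent noise between women.

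At stake are the width of the primary confidence interval, the false-positive rate of the primary test, and a choice of primary model that could still be made after the data are seen.

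**Working it through.** **1. The plan's own figure.** Inputs from section 7.2: d = 0.25, alpha 0.05 (two-sided assumed, since sidedness is not stated), power 0.85, and "We are assuming a retention rate of 88" per cent.

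n per arm = 2(1.960 + 1.036)² / 0.25² = 287.3, i.e. 288. The t-test version gives 288.3, i.e. 289, so 578 in total. Then 578 / 0.88 = 656.8, i.e. 657, which matches "We therefore plan to enroll 657 participants in the study". A one-sided test would need 231 per arm and does not match. The figure is therefore that of a two-sample comparison of independent women, with design effect 1.

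**2. What remains in the arm contrast.** Write an outcome as provider effect + window effect + individual residual. The contrast within a provider removes the provider effect. For m women per window and ICC ρ (the window's share of the variance left after provider), the variance of a window mean is σ²[ρ + (1 − ρ)/m]. A model without a window term uses about σ²/m. The ratio of the two is

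DE = 1 + (m − 1)ρ.

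Then: reported SE / true SE = 1/√DE; type I error = 2[1 − Φ(1.96/√DE)]; power at 578 with a correct SE = Φ(0.25·√(289/2)/√DE − 1.96); enrolment that restores 85% power = 578·DE/0.88, rounded up. If only Glow windows are correlated, the ICC term is halved: DE = 1 + (m − 1)ρ/2.

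Both m and ρ are assumptions; the documents give neither. For evenly filled windows:

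| m | ρ | DE | SE ratio | Type I, both arms correlated | Type I, Glow only | Power at 578 (both) | Enrolment for 85% (both) |
|---|---|---|---|---|---|---|---|
| 2 | 0.05 | 1.05 | 0.976 | 5.6% | 5.3% | 0.835 | 690 |
| 3 | 0.02 | 1.04 | 0.981 | 5.5% | 5.2% | 0.838 | 684 |
| 3 | 0.05 | 1.10 | 0.953 | 6.2% | 5.6% | 0.817 | 723 |
| 6 | 0.02 | 1.10 | 0.953 | 6.2% | 5.6% | 0.817 | 723 |
| 6 | 0.05 | 1.25 | 0.894 | 8.0% | 6.5% | 0.767 | 822 |
| 12 | 0.05 | 1.55 | 0.803 | 11.5% | 8.3% | 0.675 | 1019 |

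At ρ = 0, DE = 1 and nothing is understated.

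**3. Check by simulation.** Assumed layout: 12 providers × 8 alternating windows × 6 women = 576, provider ICC 0.02, mixed model with a provider random intercept only, 600 runs per setting (Monte Carlo error about ±1 percentage point).

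- Window ICC 0: SE ratio 1.02, type I error 4.8%.
- Window ICC 0.02: SE ratio 0.97, type I error 6.0%.
- Window ICC 0.05: SE ratio 0.92, type I error 8.2%.
- Analysis of provider-window means: type I error 4.2–4.7%.

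So the inflation comes from the missing term, and working at window level removes it.

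**4. Range over window size.** Simulations with 578 women, provider effects fitted and the window omitted, at ICC 0.02 to 0.05, gave type I error of about 5–6.5% at roughly 1.6 women per window, 5–8% at 3, 6–11% at 6 and 5–13% at 9–10. The upper ends exceed the table because they include unevenly filled windows correlated in both arms.

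**The case against.** **The broken reference is a renumbering slip.** Section 10.0 says the content of the aims did not change, so the old Aim 1 plan survives as Aim 3, and practice and provider clustering can be read across. This largely stands as to intent. But that plan was written for outcomes recorded once, at delivery. It has no baseline or repeated-measures term and refers to covariates that are never listed, so it does not define a model for PHQ-9 change at two follow-ups. It also omits the window.

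**Windows may hold very few study women.** The study schema has data collection running from November 2019 to December 2024. Allowing up to 10 months' follow-up leaves roughly 220 weeks of recruitment, or 220/6 ≈ 37 windows per provider. With the 10 sites of section 7.3 and one provider each (an assumption), that makes about 370 provider-windows, and 578/370 ≈ 1.6 women per window. Inflation is then small. This is a fair reading and belongs in the range. It does not settle the matter: it assumes every provider recruited throughout, and the Glow group size of 6–12 points to larger clusters if groups consisted mainly of study women. The documents do not say.

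**Stronger claims that a reader might infer.** One is that standard errors are certainly too small. The documents do not support that: it requires positive correlation within a window beyond what the provider shares, and no ICC is given. Another is that the window is the randomized unit and is identical to the Glow group. Strictly, the provider's starting track is randomized and the windows follow from it. The 12-woman cap also means that a Glow window can contain women from both arms.

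**Conclusion.** Both textual points hold without any assumption: the Aim 1 model is defined by itself, and no model in the plan has a term for the due-date window or Glow cohort. The effect on inference is conditional. If outcomes correlate within a provider-window beyond the provider's share, the primary standard error is too small and type I error exceeds 0.05. Under assumed ICCs of 0.02–0.05 the excess runs from negligible at 1–2 women per window to material at 6, with more if windows are larger or unevenly filled, and none at ICC 0. Correlation in the Glow arm alone roughly halves the excess. Group delivery makes some correlation plausible, but its size cannot be established from these documents. That uncertainty is a reason to prespecify the term rather than leave it out.

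**What to change.** Replace the self-reference in section 7.5 with an explicit Aim 1 linear mixed model:

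- arm, time, arm × time, site/provider, and calendar or due-date period;
- a participant-level term for the repeated measures;
- a random intercept for provider × due-date window (the Glow cohort in the Glow arm);
- small-sample degrees of freedom, such as Kenward-Roger or Satterthwaite.

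State that women sent to CPSP from a full Glow window are analysed in the arm that the protocol's allocation rule gave them, and define which window they belong to. If the window variance is estimated at zero, report that and keep the term. Point Aims 2 and 3 to this text. An arm-specific window variance is optional.

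The cost is SAP wording. Provider (section 5.1.3), due date and assignment (section 9.2) are recorded, so the window can be derived; a Glow cohort identifier is not mentioned and should be confirmed. Under the same assumptions, intervals widen by √DE: about 2% at 2 women per window with ICC 0.05 (√1.05), and 5% to 12% at 6 with ICC 0.02 to 0.05 (√1.10 to √1.25). If windows hold few women, the window variance will be weakly estimated.
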